# Effects of a low, medium, and high-intensity aquatic physiotherapy protocol on functional and biochemical parameters in individuals with knee osteoarthritis: protocol for a crossover randomized controlled trial

**DOI:** 10.12688/f1000research.140342.4

**Published:** 2024-09-16

**Keywords:** Osteoarthritis, Hydrotherapy, Protocol

## Abstract

**Background:**

Knee osteoarthritis affects the performance of daily activities, independence, and quality of life. The etiopathogenesis of this condition considers the mechanisms of activation of metalloproteinase and reactive oxygen species production pathways. Metalloproteinases-3 (MMP-3) and Glutathione Peroxidase (GPx) may be responsible for cartilage destruction. Aquatic physiotherapy promotes a positive impact on the clinical picture of osteoarthritis, and this study presents an intervention protocol that aims to evaluate the effects of a single session of different aquatic physiotherapy modalities on the biochemical and functional behavior of patients with knee osteoarthritis.

**Methods:**

This will be a crossover randomized controlled trial in which 15 individuals will be submitted to three aquatic physiotherapy modalities with a minimum 15-day wash-out period in patients over 50 years old and diagnosed with OA in at least one knee, presence of pain and at least one functional dysfunction for at least 6 months, absence of physical limitation that prevents the exercise protocol from being performed, Kellgren and Lawrence ranking between I and IV, walk independently and without auxiliary device. Variations in the concentrations of MMP-3 and GPx in peripheral blood, pain, edema, and flexibility resulting from the three aquatic physiotherapeutic interventions will be evaluated both pre- and immediate post-intervention. The reference group will be submitted to the same aquatic physiotherapy protocols, however, only the biochemical parameters and the self-perception questionnaires will be evaluated.

**Registration:**

ClinicalTrials.gov (
NCT05610696, 18/01/2023).

## Introduction

Osteoarthritis is the most prevalent rheumatologic joint dysfunction in the world, the knee joint can be considered the most affected segment and is due to local and systemic risk factors.
^
1
^ Knee osteoarthritis affects its functionality, mainly the performance of activities of daily living such as locomotion or even the transfers necessary to maintain independence and quality of life.
^
2
^
^,^
^
3
^ The evolution is generally slow and may evolve in stages or reflect as a progressive evolution over time, resulting in a worsening of the severity of the symptoms and disease,
^
4
^ which also has an important economic and social impact.
^
5
^ According to the data from

*vizhub.healthdata.org*
, Brazil is in the 15
^th^ position in the distribution ranking of osteoarthritis cases, and a prevalence of 3.42 cases per 100,000 inhabitants is estimated, with an incidence of 181.47 new cases.

Current understanding suggests that inflammatory processes are closely implicated in the pathogenesis of osteoarthritis and, in this sense, the articular cartilage, the target of degenerative processes, is modified in its composition and structure.
^
6
^ As deterioration advances, collagen fibers degrade due to the secretion of collagen-degrading enzymes known as metalloproteinases (MMPs) and the generation of reactive oxygen species (ROS), which cause oxidation and subsequent damage to articular components.
^
7
^
^–^
^
11
^

Many MMPs families have been reported to induce articular cartilage degradation.
^
7
^
^,^
^
12
^ The metalloproteinase-3 (MMP-3) can be considered the great responsible for the destruction of cartilage resulting from the degradation of several types of collagens,
^
12
^ and this same enzyme was found in the plasma shortly after articular injuries, possibly due to the inflammatory activation process of the synovium, similarly, the plasma levels of MMP-3 are shown to be predictors of articular narrowing in patients with osteoarthritis.
^
13
^ Oxidative stress arises when the intracellular generation of reactive oxygen species (ROS) exceeds the cellular capacity for neutralization, resulting in oxidative damage and potential cell apoptosis; in osteoarthritis, there is an augmented production of ROS across multiple tissue types.
^
8
^
^,^
^
14
^
^–^
^
16
^

Treatment strategies for osteoarthritis are described as evidence-based practices along with guidelines that indicate consensus of important organizations dedicated to the study of musculoskeletal conditions. Most study bases are focused on knee articulation, and, in this sense, the American College of Rheumatology (ACR),
^
17
^ The European Alliance of Associations for Rheumatism (EULAR),
^
18
^ and the Osteoarthritis Research Society International (OARSI)
^
19
^ reinforce that the practice of exercises and physiotherapy (both on the ground and in the liquid environment) are an important therapeutic arsenal for knee osteoarthritis. Although the evidence regarding the efficacy and safety of exercise is well elucidated, there is still a need to clarify the intensity levels of this activity safely. In this regard, the type of exercise and the various parameters concerning its intensity are part of the challenge for physiotherapists dedicated to rehabilitating rheumatic diseases.

It is currently well established that aquatic physiotherapy promotes a positive impact on the improvement of the clinical and functional status of patients with knee osteoarthritis, being considered an effective and safe modality once the immersion in heated water reduces overload and joint pain in addition to improving functional capacity and quality of life.
^
20
^ This treatment modality also promotes the improvement of functional capacity and emotional well-being.
^
21
^ Implementing aquatic physiotherapy for knee osteoarthritis requires considering how immersion affects exercise through forces like drag and turbulence. Thus, treatment plans should incorporate hydrostatic and hydrodynamic principles, physiological effects of immersion, and be based on individual assessments and evidence-based practices,
^
22
^ these factors confer upon aquatic physiotherapy in patients with knee osteoarthritis, a treatment strategy with fewer side effects when compared to other modalities.
^
23
^

Likewise, studies indicate that the mechanisms for this improvement are due to the interaction between the execution of the exercise with the hydrostatic and hydrodynamic principles.
^
24
^
^–^
^
26
^ However, it is still necessary to understand the impact of immersion and of different modalities of aquatic physiotherapy on the biochemical behavior of articular cartilage and correlate them with functional variables. It has recently been possible to understand the effects of an aquatic exercise program on the degenerative modifications in articular cartilage using an experimental animal model of knee osteoarthritis with an alteration in the expression of MMPs
^
27
^ and greater integrity and orientation of collagen fibers.
^
28
^ Results like these indicate the possible cellular and molecular mechanisms that justify the positive results from aquatic physiotherapy in knee osteoarthritis and reinforce the need for further studies in this area. In this context, the analysis of markers such as oxidative stress and MMPs constitutes a relevant topic of study.

Previous studies in a systematic review demonstrated that aquatic physiotherapy positively affects clinical, functional, and quality of life variables in individuals with osteoarthritis.
^
23
^
^,^
^
29
^ Similarly, it has recently been evidenced that aquatic physiotherapy positively affects pain, physical function, knee extension muscle strength, and walking ability.
^
23
^
^,^
^
30
^ These studies are related to heterogeneous protocols in intensities, frequency, total treatment time, and a single type of program.

Although this intervention has been shown to be safe, there is a lack of data evidencing its effects on biochemical variables, especially with a comparative analysis between pre-and post-intervention times, making it relevant to provide equally safe physiotherapist protocols of varying intensities. Nevertheless, understanding the central mechanism responsible for functional improvement, including the impact of aquatic physiotherapy on biochemical variables and its correlation with articular collagen degradation, will undoubtedly contribute to enhancing this type of intervention as a treatment strategy for knee osteoarthritis through evidence-based practices. These factors confer upon aquatic physiotherapy in patients with knee osteoarthritis a treatment strategy with fewer side effects than other modalities.

Therefore, the protocol proposed in this study presents different modalities of intervention in aquatic physiotherapy, this being a single session, considering low, medium, and high-intensity strategies, seeking to evaluate its effects on the biochemical and functional behavior of patients with knee osteoarthritis. It aims to identify possible variations in the concentration of the MMP-3 subfamily and the oxidative stress marker Glutathione Peroxidase (GPx) in peripheral blood, assess pain, edema, and flexibility in patients with knee osteoarthritis and in response to different aquatic physiotherapy interventions. Therefore, understanding the appropriate exercise intensity, coupled with understanding its effects on biochemical mediators directly involved in the genesis of osteoarthritis, can provide confidence for the prescription and execution of therapeutic exercises under immersion in aquatic physiotherapy treatment. These strategies may increase treatment adherence, prevent symptom exacerbation, minimize adverse effects, and provide greater therapeutic safety.

## Methods

### Trial design

This is an interventional transversal study, randomized clinical trial, crossover type with three arms: low, medium, and high-intensity aquatic physiotherapy.

This clinical intervention protocol follows the recommendation from the Standard Protocol Items: Recommendations for Interventional Trials (SPIRIT).
^
31
^
^,^
^
32
^ The study sample, defined according to criteria, will be submitted to a single session of each one of the following modalities of aquatic physiotherapy: (a) low-intensity, (b) medium-intensity, and (c) high-intensity. Among each modality, a minimum of a 15-day wash-out period will be respected, in accordance with
Figure 1.

**Figure 1. f1:**
[figure not shown]
Flow of interventions and assessment parameters.

For this study, 15 participants will be recruited. The sample size calculation indicated a non-centrality parameter (δ) of 3.8, suggesting a moderate effect on biomarker variations. The critical t-value was 2.10, with degrees of freedom (df) of 16.143, resulting in a total sample size of 15 participants and an actual power of 0.95. The effect size calculation was based on means and standard deviations, and for our main dependent variables, these were reported by previous investigations: Germanou
^
33
^ through the antioxidant levels and Nascimento
^
34
^ through the MMP-2 and MMP-9 analysis between the control and intervention group, in this case, it is represented by patients with knee osteoarthritis.

The assessment parameters used in each variable will consist of instruments that allow for the assessment of the variations in the MMP-3 concentration, oxidative stress, pain, edema, and flexibility. In addition, a self-perception questionnaire, developed by the authors, will be applied to assess self-perception. It consists of a Likert scale where the patient must classify their perception of well-being between zero and 10, where zero represents the worst feeling of well-being and 10 represents the best feeling of well-being. The data collection form, informed consent form and patient identification form can be found as
*Extended data.*
^
32
^ The trial has been registered on
ClinicalTrials.gov (
NCT05610696, 18/01/2023).

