### Statistical analysis

The resulting data will be tabulated, considering the absolute values and their respective standards. Information regarding the main outcome corresponding to the variations in the concentrations of MMP-3 and GPx in peripheral blood due to three different aquatic physiotherapy interventions will be comparatively evaluated among the distinct interventions and among the different times (in pre- and post-intervention moments).

The information on the outcome regarding pain, edema, and flexibility will be comparatively assessed among the different types of intervention. Statistical analyses will be performed in the SPSS software and will be considered as a significance level when p>0.05 through the repeated measures ANOVA statistical test.

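### The sample-size paragraph contradicts itself and does not fit the crossover: 15 people cannot give 16.143 degrees of freedom, a non-centrality parameter of 3.8 is not a moderate effect, and the planning contrast is not between intensities

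*Protocol article*

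**What the plan says.** The sample-size paragraph is in the protocol article under Methods, Trial design, just after Figure 1. It reports a "non-centrality parameter (δ) of 3.8, suggesting a moderate effect on biomarker variations". It puts the critical value of t at 2.10. The remaining figures are given as "degrees of freedom (df) of 16.143, resulting in a total sample size of 15 participants and an actual power of 0.95". It says the effect size was built from means and standard deviations in two earlier studies, one on antioxidant levels and one that enters "through the MMP-2 and MMP-9 analysis between the control and intervention group". It names no test.

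The design it is meant to support is a "crossover type with three arms: low, medium, and high-intensity aquatic physiotherapy". The abstract says that "15 individuals will be submitted to three aquatic physiotherapy modalities". The Statistical analysis section gives the main outcome as "variations in the concentrations of MMP-3 and GPx in peripheral blood due to three different aquatic physiotherapy interventions", compared among interventions and among times by repeated measures ANOVA at the 5% level.

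**The concern.** The figures in this paragraph should all come from one calculation for one test, and they do not fit together. The degrees of freedom exceed what 15 people can supply, and the critical value does not belong to those degrees of freedom. A non-centrality parameter grows with the sample size, so it is not an effect size and cannot be called moderate by itself.

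The calculation also answers a different question. A control-versus-intervention difference shows how far an exercised group departs from a control group. This trial asks whether three active intensities differ from one another in the same people. A large effect of the first kind does not imply one of the second kind, and the article gives no between-intensity difference, within-person SD or correlation that would link them.

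This is the article's only justification for 15 participants. A reader will take from it 95% power to detect a moderate difference. If the intensities then show no clear difference, that statement invites the conclusion that intensity does not matter, which a study of this size may not be able to support.

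**Working it through.** **Inputs from the article.** Non-centrality parameter δ = 3.8, df = 16.143, critical t = 2.10, total N = 15, power 0.95 (Trial design); significance level 0.05 (Statistical analysis). Sidedness is not stated; I take it as two-sided, because the one-sided critical value at 16.143 df would be 1.745, far from 2.10.

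**Step 1: reproduce the stated power.** Power = P(|T| > t_crit), with T noncentral t with the given df and δ.

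| df | two-sided 5% critical t | power at δ = 3.8 |
|---|---|---|
| 16.143 | 2.118 | 0.946 |
| 14 | 2.145 | 0.942 |
| 13 | 2.160 | 0.939 |

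The stated 0.95 is reproduced to within about one percentage point in every row. It follows from δ.

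**Step 2: degrees of freedom against N = 15.**
- Paired or one-sample: 15 − 1 = 14.
- Two groups, equal variances: 15 − 2 = 13; the Welch version gives at most 13.
- Rank-test versions scale N by an efficiency factor (3/π, π²/9, 1.5 or 0.864) before subtracting 1 or 2. At N = 15 the signed-rank form gives 13.32, 15.45, 21.5 or 11.96, and the Mann-Whitney form gives 12.32, 14.45, 20.5 or 10.96.

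None of these is 16.143.

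**Step 3: the critical value.** At 16.143 df it is 2.118. The printed 2.10 belongs to about 18 df (2.101 at exactly 18). With 2.10 in place of 2.118, power at 16.143 df moves only from 0.946 to 0.948, so this is minor.

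**Step 4: effect size implied by δ = 3.8 at N = 15.**
- Paired: dz = δ/√N = 3.8/√15 = 0.98.
- Two groups of 7 and 8: d = δ/√(n1·n2/(n1 + n2)) = 3.8/√(56/15) = 3.8/1.932 = 1.97.

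On the usual convention (0.5 medium, 0.8 large), both are large.

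**Step 5: what 15 participants deliver.** One within-person contrast of two intensities, paired t-test, df = 14, δ = dz × √15. The dz values are illustrative assumptions; the article gives none. The Bonferroni column uses α = 0.05/3 for three pairwise contrasts, with critical t 2.718 in place of 2.145.

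| assumed dz | δ | power, α = 0.05 | power, α = 0.05/3 |
|---|---|---|---|
| 1.0 | 3.87 | 0.95 | 0.86 |
| 0.78 | 3.02 | 0.80 | 0.62 |
| 0.5 | 1.94 | 0.44 | 0.26 |

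For scale, 95% power at dz = 0.5 with a single unadjusted contrast would take 54 people.

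**Step 6: planning contrast against trial contrast.**

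| | sample-size paragraph | trial |
|---|---|---|
| comparison | control versus intervention group | three intensities, within person |
| markers | antioxidant levels; MMP-2 and MMP-9 | GPx; MMP-3 |
| test | t-type (δ, critical t, df) | repeated measures ANOVA |

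**The case against.** The strongest defence is that the power value is right. Given δ = 3.8, power is about 0.94 to 0.95 whether the df are 13, 14 or 16.143, so the df inconsistency by itself costs less than one percentage point. That stands. A reader might infer that 0.95 is a calculation error, and it is not.

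The second defence is that planning from published proxy markers is common and is disclosed here. Antioxidant levels are a plausible stand-in for GPx, one of the two main markers. That also stands; the weight of the criticism falls on the type of contrast more than on the choice of marker.

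Third, 0.44 depends on reading moderate as dz = 0.5 and on a single paired t-test, whereas the plan is a repeated measures ANOVA. This is fair, and the figures are labelled accordingly. It does not rescue the statement, because δ = 3.8 in 15 people corresponds to a large difference under either reading.

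It is tempting to go further and say where the figures came from. A two-group rank test with 19 people gives 19 × 3/π − 2 = 16.144, close to the printed df, and 21 people with factor 0.864 gives 16.144 as well. The article names no test, two candidates fit equally well, and neither has 15 people. A two-group origin is therefore an assumption only, and the point does not rest on it.

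Nor do the documents show that no MMP-3 variance was available for planning, since the article says means and SDs for its main variables were taken from earlier work. The unstated size of the reference group may simply have been left to the full protocol.

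**Conclusion.** The point holds in this form: the sample-size paragraph is internally inconsistent and does not describe this trial. The df cannot come from 15 people under the paired, two-group or standard rank-test calculations checked. The effect labelled moderate is large (dz 0.98 or d 1.97). The planning inputs do not support δ = 3.8 for differences between intensities. Power of 95% for a moderate effect is not delivered; at an assumed dz of 0.5 it is 0.44 for one contrast, and 0.26 with Bonferroni correction over three.

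These power figures assume a two-sided 5% level, all 15 participants contributing to the contrast, and a paired t-test. They are not the power of the omnibus ANOVA.

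A reader might infer that the trial is too small and must recruit more. The documents do not establish that. They present the study as exploratory and as a guide for later longitudinal work, and 15 may be adequate for that purpose if its sensitivity is stated correctly. The correction is still needed, because the printed statement is wrong as it stands and no further document could make it right.

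**What to change.** Keep N = 15. Delete the description of the effect as moderate, the 16.143 df and the 2.10 critical value. Replace them with wording along these lines:

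*Fifteen participants with knee osteoarthritis will be included. For a within-person contrast of two intensities (paired t-test, 14 df, two-sided 5% level), this gives power of 0.95, 0.80 and 0.44 for assumed standardised differences dz of 1.0, 0.78 and 0.5. With Bonferroni correction over the three pairwise contrasts, the corresponding values are 0.86, 0.62 and 0.26. These are single-contrast figures, not the power of the omnibus repeated measures ANOVA. The effect used in planning came from a control-versus-intervention comparison of antioxidant levels and of MMP-2 and MMP-9, not from a difference between intensities.*

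The text should not claim that MMP-3 variability was unavailable, nor name a test as the source of the old df unless the original calculation is found.

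The cost is a protocol wording change. No participants, visits or assays are added, and the article lists the study as not yet recruiting, so the change can be made before data exist. The price is a less favourable power statement.

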### Study setting

The study population corresponds to people with knee osteoarthritis. The population will be recruited from physiotherapy services from University Feevale.

The protocol will be performed in the facilities of the Aquatic Physiotherapy sector. The swimming pool has accessibility
*via* stairs and a ramp with appropriate handrail support. Heating is provided by an electronic boiler fed with liquefied petroleum gas that guarantees minimum temperature variations (33°C and 34°C) measured with a submerged mercury column thermometer. The swimming pool depth varies between 100 and 150 cm, transitioned by means of a ramp; the entire swimming pool is lined with non-slip tiles. The swimming pool also has two hydromassage spaces on one of the borders. Each one is equipped with hydromassage jets, one in the trunk support region and two on the sides of this area.

### Eligibility criteria

The following eligibility criteria will be considered: being over 50 years old and diagnosed with osteoarthritis in at least one knee according to the American College of Rheumatology
^
35
^ criteria, referring to pain and at least one dysfunction for at least six months, absence of physical limitation that prevents the performance of the exercises protocol, have Kellgren and Lawrence classification between III and IV
^
36
^ and independent gait. Subjects who present autoimmune inflammatory conditions, use of psychotropic, immunosuppressant, or steroids drugs, consumption of antioxidants (vitamin E, statins, or uric acid reducers), alcohol and tobacco, progressive ankylosis states, the coexistence of neurological lesions, infections or skin diseases that contraindicate swimming pool immersion, surgical procedures on the knee joint in the last 12 months (excluding meniscectomy or arthroscopy), lower limb articular prosthesis, presence of inflammatory or infectious disease, uncontrolled systemic arterial hypertension, uncontrolled diabetes, chronic obstructive pulmonary disease and history of ischemic heart disease, self-reported aquatic phobia, and chlorine allergy will be excluded from the study. For control purposes, a reference group will be constituted with age matching and exclusion criteria identical to the experimental group.

